## Abstract

**Background.:**

BK polyomavirus (BKPyV) is a common opportunistic infection in kidney transplant recipients, typically reactivating in the context of immunosuppression. Although asymptomatic in immunocompetent individuals, reactivation in transplant recipients can cause BKPyV-associated nephropathy (BKPyVAN), a leading cause of graft dysfunction and loss. BKPyV viremia affects approximately 10%–15% of transplant recipients, and once BKPyVAN is established, the risk of graft failure can exceed 50%. The current standard of care involves immunosuppression reduction to restore virus-specific immunity, but this approach increases the risk of acute and chronic rejection. Intravenous immunoglobulin (IVIg), which contains antiviral and immunomodulatory antibodies, has been proposed as an adjunctive therapy, although evidence supporting its efficacy remains limited to small observational studies.

**Methods.:**

The BEAT-BK trial is a multicenter, adaptive, randomized controlled trial comparing standard immunosuppression reduction with or without IVIg in kidney and simultaneous pancreas-kidney transplant recipients with BKPyV viremia or biopsy-confirmed BKPyVAN. The trial will enroll participants aged 2 y and older, randomizing them 1:1 to receive standard care alone or in combination with a total IVIg dose of 2 g/kg for 8 wk. An adaptive Bayesian design will permit interim analyses with the potential for early trial success or futility.

**Results.:**

The primary endpoint is a composite ordinal outcome at 12 wk, incorporating death, graft loss, estimated glomerular filtration rate decline, acute rejection, viral load, and degree of immunosuppression reduction. Secondary outcomes include viral clearance, development of BKPyVAN and donor-specific antibodies, infections, malignancy, quality of life, and cost-effectiveness.

**Conclusions.:**

This trial will provide the first high-quality evidence on the role of IVIg in BKPyV management and inform clinical decision-making in posttransplant care.

## INTRODUCTION

BK polyomavirus (BKPyV) infection is a rare but devastating complication in kidney and simultaneous pancreas-kidney (SPK) transplant recipients. The overall incidence of BKPyV DNA in the blood (BKPyV-DNAemia) is approximately 10%–15%, with polyomavirus-associated nephropathy (BKPyVAN) occurring in approximately 5% of recipients within the first 12 mo posttransplant.^1,2^ BKPyV is a ubiquitous infection, typically acquired in childhood,which establishes latency in the native epithelial cells.^3^ Reactivation and progression to BKPyVAN occur exclusively in immunocompromised individuals.^4^ BKPyV DNAemia, detected by real-time polymerase chain reaction and leading to kidney dysfunction and BKPyVAN, is the fourth leading cause of graft loss among kidney and SPK transplant recipients worldwide. Once established, BKPyVAN carries a >50% risk of graft loss within 5 y.^5^

The strongest risk factor for BKPyV reactivation and disease is over-immunosuppression, particularly in the early posttransplant period. Other risk factors include the use of T-cell depleting agents, increased exposure to tacrolimus, older recipient or donor age, and male sex.^2,6^ Currently, apart from judicious reduction of immunosuppression, no effective interventions are available for treating BKPyV infections. Although adjuvant therapies are not commonly used, rescue treatments such as intravenous immunoglobulin (IVIg) have been used in patients with uncontrolled viraemia and ongoing graft deterioration when conventional immunosuppression reduction has failed. IVIg is a nondepleting agent containing natural antibodies with potential antiviral and immunomodulatory properties.^7^ It is used against some chronic infections (Epstein-Barr virus) and for the treatment of antibody-mediated rejection in kidney transplantation.^8^ However, in BKPyV infection, the certainty of the evidence for IVIg is very low because of imprecision and a high risk of bias (small, case series, retrospective cohorts). Still, it holds promise based on findings from observational data. In a single center, cohort study, recipients with BKPyV DNAemia who received IVIg as adjuvant therapy were more likely to achieve complete viral clearance at 12 mo (77.3% versus 33.3%, *P* < 0.01) and less likely to relapse (11% versus 27.3%, *P* = 0.01) compared with recipients who received conventional therapy alone.^9^ Therefore, high-quality trial-based evidence is needed to determine whether IVIg provides meaningful patient-relevant and clinically beneficial effects over standard care in kidney and SPK transplant recipients with BKPyV infections.

The BEAT-BK trial will evaluate the efficacy of immunosuppression reduction strategies, with and without the addition of IVIg, in kidney and SPK transplant recipients with BKPyV infection. The trial will assess the effects of these strategies on key clinical outcomes, including the severity of BKPyV infection, kidney allograft function, allograft loss (kidney and/or pancreas), acute transplant rejection, the degree of immunosuppression reduction required, and mortality.

### Protocol Design and Methods

This study is a multicenter, adaptive, 2-arm randomized trial designed to compare standard-of-care immunosuppression reduction or modification, with and without the addition of IVIg, in kidney and SPK transplant recipients with BKPyV infection. The trial is structured to assess multiple outcomes in parallel, including viraemia, acute rejection, immunosuppression load, allograft function and adverse events (AEs). The trial will employ an adaptive design with prespecified interim analyses, allowing for the potential to stop for early success or futility. The trial will use a Bayesian hierarchical modeling strategy to facilitate the empirical borrowing of information across related subgroups. This approach enables more efficient estimation of subgroup-specific intervention effects.^10^

### Study Setting

Patients will be recruited from kidney transplant units across Australia as well as from international sites including New Zealand, Canada, and the United States.

### Eligibility Criteria

To be eligible for trial inclusion, the patient must meet all of the following criteria:

Aged 2 y or older.Received a kidney or SPK transplant.Have BKPyV DNAemia, confirmed by real-time polymerase chain reaction calibrated to the World Health Organization international standard, with a viral load ≥ 5 × 10^3^ copies/mL (or equivalent 3.7 log_10_ copies/mL), or histologically confirmed BKPyVAN, within 3 wk before randomization.Be legally capable of providing informed consent, or have consent provided by a parent, guardian, or other legally authorized representative (for patients younger than 18 y).

To be eligible, the patient must not meet any of the following criteria:

Presence of contraindications to IVIg treatment.Current active acute rejection or rejection within the past 3 mo.Considered by the treating clinician to be unsafe to enroll.Estimated life expectancy of <12 mo.Receiving belatacept as part of their immunosuppression regimen.Currently receiving, or previously having received, virus-specific T-cell infusions for BKPyV infection.History of prior IVIg therapy for BKPyV DNAemia during the current transplant.IVIg therapy for any indication within 4 wk before randomization.

### Consent

Initial ethics approval for this trial was granted by Metro South Health Research, Queensland Government, Australia (HREC/2022/QMS/87487). Informed consent will be obtained before the initiation of any trial procedures, following approval of site-specific consent forms by the appropriate independent ethics committee. For pediatric participants, consent will be obtained from a parent or guardian. Where appropriate, children will also be provided with age-appropriate information and invited to cosign the consent form if judged sufficiently mature.

### Intervention

Participants will be randomized to 1 of 2 treatment arms: standard immunosuppression reduction alone or immunosuppression reduction in combination with IVIg. The total intended IVIg dose over the 8-wk intervention period will be 2 g/kg, with a tolerance range of 1.8–2.2 g/kg. The recommended dosing schedule is 250 mg/kg weekly for 8 wk, with a 2-wk administration window for flexibility. The first dose of IVIg must be given within 14 d of randomization. Because of potential supply and logistical constraints, the protocol permits IVIg doses to be combined, allowing for up to 2 doses (up to 500 mg/kg) to be administered during a single session.

In both arms, immunosuppression reduction is implemented per current standard of care following a standardized algorithm adapted from the 2024 Transplantation Society guidelines (Table 1).^11^ This typically involves a stepwise reduction in calcineurin inhibitors (CNIs) and antiproliferative agents, or conversion to less potent agents. The protocol provides flexibility for clinicians to alter immunosuppressive therapy according to local standards and clinical judgment. The treatment goal is to achieve a BK viral load <1000 copies/mL, where feasible.

**TABLE 1. T1:** Recommended approach to immunosuppression reduction (adapted from The Second International Consensus Guidelines on the Management of BK Polyomavirus in Kidney Transplantation, 2024^11^)

Strategy 1: Antimetabolite is reduced first
Reduction of the dose of antimetabolite by at least 50%
We suggest further immunosuppression reduction if BKPyV DNAemia does not decrease by 10-fold at 4 wk or does not clear below lower limit of detection as follows:
Discontinuation of the antimetabolite and tapering of corticosteroid dose to 5–10 mg/d of prednisone or equivalent, if applicable
We suggest adding prednisone (or equivalent) 5–10 mg/d for patients who are not on corticosteroids to avoid CNI monotherapy
If further decrease in immunosuppression is necessary, we suggest a stepwise reduction of the CNI dose (tacrolimus trough target 5 ng/mL; cyclosporine trough target 100 ng/mL)
Strategy 2: CNI is reduced first
Reduction of the dose of CNI by 25%–50% in 1 or 2 steps to target trough concentrations of tacrolimus of 3–5 ng/mL and cyclosporine trough concentrations of 75–125 ng/mL)
We suggest further immunosuppression reduction if BKPyV DNAemia does not decrease by 10-fold at 4 wk or does not clear below lower limit of detection as follows:
Reduction of the antimetabolite by 50% and tapering of corticosteroid dose to 5–10 mg/d of prednisone or equivalent, if applicable
Discontinuation of the antimetabolite
We suggest adding prednisone (or equivalent) 5–10 mg/d for patients who are not on corticosteroids to avoid CNI monotherapy

BKPyV, BK polyomavirus; CNI, calcineurin inhibitor.

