### Randomization and Blinding

Participants will be randomized in a 1:1 ratio using a secure, web-based randomization system embedded within the REDCap trial database. Randomization will be stratified by age, country, and transplant type (kidney alone or SPK), with the use of random permuted blocks to ensure balanced allocation across treatment groups within each center.

Given the nature of the intervention, complete blinding is not feasible. Therefore, clinicians and participants will be unblinded to the treatment allocation. However, measures are in place to preserve blinding among other key stakeholders. The BEAT-BK Global Steering Committee (GSC), site investigators, and the Trial Management Committee will remain blinded to individual treatment allocations and any aggregate data that could compromise unblinding of study outcomes. Although the statistical analysis team will be unblinded during interim analyses, a designated trial statistician will remain blinded throughout to support final primary analysis. All enrolled participants will be followed for a total of 48 wk after randomization.

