Reductions in immunosuppression will be defined as minimal, moderate, or large, depending on the degree of immunosuppression reduction required at 12 wk postrandomization (Table 3). The largest reduction in any single immunosuppressive medication (excluding steroid therapy) will be considered for outcome classification. Reductions in antimetabolites will be categorized according to the percentage reduction relative to initial dosing. Reductions in tacrolimus, ciclosporin, and mammalian target of rapamycin (mTOR) inhibitors will be categorized as the reduction in trough target levels at 12 wk relative to initial target trough levels. For patients receiving tacrolimus, ciclosporin, and mTOR inhibitors, their treating clinicians will be asked to specify target levels at randomization and again at 12 wk. Reductions in steroid dosing will not be considered part of the ranked outcome. Substantial variation exists between centers in the use of steroids after transplantation, with some centers adopting steroid-free programs. Therefore, in this cohort, reductions in steroid doses may be unrelated to BKPyV infections.

**TABLE 3. T3:** Classification of immunosuppression reduction by degree of reduction

Immunosuppression medication	Degree of reduction^*a*^	Large	Moderate	Minimal
Antimetabolite	Dose reduction from baseline (%)	≥75%	>25–<75%	≤25%
Ciclosporin (C0 or C2)	Target-level reduction from baseline (%)	≥75%	>25–<75%	≤25%
mTOR-I (trough)				
Tacrolimus (trough, ng/mL)	Baseline trough	Final target trough	Final target trough	Final target trough
	≥8	≤3.9 (or cessation)	4–6.9	≥7
	6–8	≤3.9 (or cessation)	4–5.9	≥6
	4–6	≤2.9 (or cessation)	3–3.9	≥4
	<4	Cessation	≤2.9 (>0)	≥3

^*a*^ The largest reduction in any single immunosuppressive medication (excluding steroid therapy) will be considered for outcome classification.

mTOR, mammalian target of rapamycin.

In addition to dose reductions, conversion from a more potent to a less potent immunosuppressive agent in direct response to BKPyV infection will be classified as a “large” reduction. Conversions performed for other indications, such as drug intolerance, adverse effects, or malignancy, should not be considered a “large” reduction.

Conversions that qualify as “large” immunosuppressive reductions include:

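### The two permitted taper strategies can place the same viral course in different primary-outcome categories, and an unblinded clinician may choose between them after allocation

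*Protocol article*

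**What the plan says.** **Strategies (Intervention, Table 1).** Strategy 1 starts with "Reduction of the dose of antimetabolite by at least 50" per cent; its next step is "Discontinuation of the antimetabolite and tapering of corticosteroid dose to 5–10 mg/d of prednisone or equivalent, if applicable". Strategy 2 starts with "Reduction of the dose of CNI by 25%–50% in 1 or 2 steps to target trough concentrations of tacrolimus of 3–5 ng/mL"; its next step is "Reduction of the antimetabolite by 50% and tapering of corticosteroid dose to 5–10 mg/d of prednisone or equivalent, if applicable", and stopping the antimetabolite is listed after that. The trigger for going further is worded identically in both: "We suggest further immunosuppression reduction if BKPyV DNAemia does not decrease by 10-fold at 4 wk", or if the virus does not clear below the detection limit. The text above the table lets clinicians alter therapy by local standards and judgment.

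**Scoring (Primary Outcome, Table 3).** "The largest reduction in any single immunosuppressive medication (excluding steroid therapy) will be considered for outcome classification". For an antimetabolite, a cut of 75% or more is Large, above 25% and below 75% Moderate, and 25% or less Minimal. Ciclosporin uses the same percentages on target level. Tacrolimus is scored on the final target within bands of baseline trough. Baseline is the time of randomization. Treating clinicians specify the target levels at randomization and at 12 weeks.

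**Blinding and analysis.** Randomization and Blinding states that "clinicians and participants will be unblinded to the treatment allocation". Strata are age, country and transplant type. Statistical Analyses adjusts for site and other relevant covariates, and acts on the posterior probability that the common odds ratio is below 0.9 (success above 95%, futility below 10%).

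**The concern.** Categories 1–3 are meant to record how much immunosuppression reduction a patient required, and the article treats a small reduction as a sign of viral control. Under the largest-single-drug rule they also record which drug was cut first. That alone adds noise. It becomes bias if the choice of strategy depends on the arm, which an open-label design with stated flexibility permits. Adjustment for site absorbs centre habit, but not a choice made differently by arm within a site. The one immunosuppression sensitivity analysis described (Secondary Outcomes) changes the baseline regimen, not the strategy. At stake is a shift in the common odds ratio, near a decision value of 0.9, that does not come from IVIg.

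**Working it through.** **The plan's own figures.** The look schedule is consistent: 100 + 3 × 60 = 280, the stated maximum. The article gives no category distribution, target odds ratio or power, so the sizes below rest on stated assumptions.

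**Second step** (further reduction triggered, load at or below 1000 copies/mL at week 12, no rejection or category 5 event).
- Strategy 1: antimetabolite stopped, a 100% cut. Large, category 3, always.
- Strategy 2: antimetabolite cut by 50%. Moderate, category 2, unless the CNI step was already Large or the antimetabolite is later stopped.

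**First step, taken after randomization.**
- Strategy 1: a cut of 50% to under 75% is Moderate and 75% or more is Large. Category 1 cannot be reached while the cut stands.
- Strategy 2, tacrolimus: assume trough moves in proportion to dose, so target = baseline × (1 − cut), with the cut between 25% and 50% and the target between 3 and 5 ng/mL.
  - Baseline 4 to about 5.3: Moderate (for example 5 to at most 5 × 0.75 = 3.75).
  - Minimal needs a target of at least 4, so baseline of at least 4 / 0.75 = 5.33, and below 6.
  - Baseline above 6 and below 8: Large if the target is 3.9 or less (for example 7 × 0.5 = 3.5), otherwise Moderate.
  - Baseline above 8: the lowest target exceeds 8 × 0.5 = 4.0, so Moderate. (Table 3's bands overlap at exactly 6 and 8.)
- Strategy 2, ciclosporin: Minimal at exactly 25%, Moderate above that to 50%.

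So a prompt responder on Strategy 2 may score better than, the same as, or worse than one on Strategy 1.

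**Effect on the odds ratio with no IVIg effect.** Let r be the share of participants in categories 1–3 (assumed 40% or 60%), s the share of an arm using Strategy 1, and S1, S2 the assumed splits across categories 1/2/3. Then P(category k) = r × [s × S1k + (1 − s) × S2k] for k = 1, 2, 3, with categories 4 and 5 equal in both arms. Take s = 0.6 in controls and 0.4 with IVIg.

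Example using the second-step difference alone (S1 0/50/50, S2 0/80/20, r = 0.6):
- Control: category 2 = 0.6 × (0.6 × 0.5 + 0.4 × 0.8) = 0.372; category 3 = 0.6 − 0.372 = 0.228.
- IVIg: category 2 = 0.6 × (0.4 × 0.5 + 0.6 × 0.8) = 0.408; category 3 = 0.192.

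A two-arm proportional-odds fit gives 0.93.

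| S1 | S2 | OR, r = 40% | OR, r = 60% |
|---|---|---|---|
| 0/60/40 | 5/60/35 | 0.99 | 0.98 |
| 0/60/40 | 10/65/25 | 0.98 | 0.95 |
| 0/50/50 | 0/80/20 | 0.97 | 0.93 |
| 0/60/40 | 40/45/15 | 0.95 | 0.89 |

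Reversing the imbalance in the third row gives 1.03 and 1.07.

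**Effect on the stopping rule.** A separate simulation used 5000 null trials per scenario, looks at 100, 160, 220 and 280, and a standard Gaussian prior on the log odds ratio, without covariates or loss to follow-up. It assumed 35–60% in categories 4–5, 40–60% of the rest needing one step only, 0–30% of Strategy 2 one-step cases Minimal, and 25–50% of its second-step cases Large.

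| Strategy 1 use, IVIg vs control | OR | False success |
|---|---|---|
| Same mix | 1.00 | 3.7–4.5% |
| 40% vs 60% | 0.87–0.98 | 4.4–11.3% |
| 30% vs 70% | 0.76–0.96 | 5.3–26.9% |

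**Does adjustment for a declared strategy cure it?** Let strategies be declared 50/50 in both arms, with later departures producing 60% versus 40% use. Under the table's last row the odds ratio is about 0.95 (r = 40%) and 0.89 (r = 60%), both before and after adjustment for the declaration.

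**The case against.** The strongest replies, and what stands of each:

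- **The first step does not favour Strategy 2 in general.** This stands. A reader might infer that a prompt responder always scores better there. The 25% minimum cut confines Minimal to baselines of about 5.3 to under 6 (or ciclosporin at exactly 25%), and some baselines between 6 and 8 come out Large.
- **Escalation can end Large under both strategies.** This stands in part: Strategy 2 also lists stopping the antimetabolite. But it lists a 50% cut before that, and Strategy 1 does not.
- **Some first steps precede randomization.** This stands. The qualifying result may be up to 3 weeks old, and a change already made is not scored against the randomization baseline, so category 1 is then reachable under Strategy 1.
- **The 0.89 figure needs a large category 1 share.** For that row this stands: with 10% of Strategy 2 patients in category 1, the range is 0.98 to 0.95. The second-step difference alone still gives 0.97 to 0.93.
- **No evidence of arm-dependent choice.** This stands. A reader might infer that the trial is biased towards IVIg. The article shows only that the choice is open, and the direction could be the reverse.
- **The full protocol may fix the strategy beforehand.** Possible. The article's wording on flexibility and judgment points the other way. It also says that site investigators stay blinded to individual allocations, which sits awkwardly with unblinded clinicians setting the scored targets.

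**Conclusion.** The point holds in limited form. The second-step difference of one category follows directly from Tables 1 and 3, subject to the two exceptions above. The first-step difference is conditional and has no fixed direction. Participants with more than 1000 copies/mL, rejection or a category 5 event are unaffected. If both arms use the same mix of strategies, the cost is noise and, for post-randomization Strategy 1 patients, loss of category 1; the null is not biased.

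If the mix differs by arm at 60/40, the null odds ratio is roughly 0.98 to 0.89, with 0.99 and 0.87 at the outer edges of the assumptions tried. These sizes rest on assumed category splits, an assumed imbalance and trough proportional to dose; none comes from the article. A reader might also infer that adjusting for a pre-declared strategy removes the bias. It does not, because the bias arises from departures after allocation. This is a cheap improvement worth making, not a flaw that invalidates the design.

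**What to change.** 1. Add one mandatory REDCap field, completed before allocation is revealed: the taper strategy intended for this patient (1, 2 or other). It cannot be reconstructed reliably later.
2. Report strategy used, and departures from the declared one, by arm. This makes an arm-related choice measurable.
3. Prespecify a sensitivity analysis of the primary model with categories 1–3 merged. Strategy-dependent scoring then cancels: with no IVIg effect the merged odds ratio is 1 in every scenario of the table above.
4. Adjustment for declared strategy is optional. It offers a small precision gain and does not correct departures.

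**Cost.** One data field, a slightly earlier decision by sites, and one extra analysis with less information. On the approximation that information is proportional to 1 − Σp³, assume 50%, 35% and 15% in categories 1–3, 4 and 5, with the first group split 0/65/35. Five levels give 1 − (0.325³ + 0.175³ + 0.35³ + 0.15³) = 0.914; merged gives 1 − (0.5³ + 0.35³ + 0.15³) = 0.829, a loss of about 9%. The merged analysis also cannot see a genuine immunosuppression-sparing benefit, so it supports the primary analysis and does not replace it. Clinicians keep their present freedom over the taper.
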